### Interventions

2.4

Participants were randomized in a 1:1 ratio to either high-dose rivaroxaban 15 mg twice daily (film-coated tablets to be taken orally with food) or high-intensity warfarin, target INR 3.5 (range, 3.0-4.0) for 24 months. Participants on warfarin require INR monitoring by an appropriate anticoagulation clinic in line with usual practice. Adherence to trial medication is assessed by completion of the Medication Adherence Rating Scale (MARS) at each follow-up visit. In addition, for participants on warfarin, INR documentation is reviewed.

The Supplementary File provides further information relating to interventions, including safety processes to mitigate bleeding risk and criteria for anticoagulation review ± modification during trial (including bleeding and thrombosis, weight change, and moderate/severe renal impairment).

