### Sample size

2.7

The study sample size target was a minimum of 40 participants. RISAPS is a noninferiority trial. Previous research has suggested that noninferiority margin should be half the SD of the primary outcome from historical studies. Accordingly, sample size calculations are based on a study by Benjamin et al. [29]. This used data from the prospective St George’s Cognition and Neuroimaging in Stroke study of patients with symptomatic lacunar stroke and confluent leukoaraiosis (*n* = 121) to determine sensitivity of MRI to change in small vessel disease (SVD) and calculate sample size estimates for a clinical trial. The mean slope (ie, annual rate of change of WMH volume expressed as a percentage of brain volume) was an increase of 0.8% (95% credible interval, 0.67%-0.95%), with a SD of 0.5. To perform a sample size calculation for RISAPS, we have therefore chosen a noninferiority limit of 0.25, ie, the smallest difference in mean slopes between the two groups that would lead us to conclude inferiority. Our noninferiority limit corresponds to half the between-patient variability in slopes. With the planned sample size of 40, we would be able to establish noninferiority based on approximately 50% of this change (a mean increase of 0.4% per year). We have applied a more liberal type I error rate (alpha, falsely declaring a difference when one does not exist) of 10%, which is in line with most phase IIb trials, given that they are not confirmatory in nature.

In practice, 95% CI for WMH volume change will be ±0.32, given the expected SD of 0.5, due to the use of fully observed data as opposed to the formal sample calculation, which adjusted for power of 80%.

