### Statistical methods for analyzing primary and secondary outcomes

2.11

The primary outcome will be analyzed using a linear mixed effects model to compare the mean rate of change in WMH volume over time between the two randomized groups. This will allow estimation of average slope in each group with respective 95% CIs, while allowing for variability between individuals within each group. Interparticipant clustering will be modeled by fitting a random intercept model, and measurement of differences in rates of WMH volume changes for each participant will be facilitated by introducing a random slope. The primary model will not include explanatory variables apart from the minimization variable. The fixed effects will include randomized groups only. We will restrict the sample to those who have completed the study and provided data for two MRI scans, as we do not feel that the assumptions of Missing At Random (MAR) or Missing Completely At Random (MCAR) are appropriate in this clinical context.

Further details are provided in the Supplementary File, including (i) methods for additional analyses (eg, subgroup and adjusted analyses) and (ii) definition of analysis population relating to protocol nonadherence and statistical methods to handle missing data.

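### Section 2.7 pairs a 0.25 limit, a 10% alpha of unstated sidedness and a 95% CI of ±0.32 that do not fit together; N=40 has 80% power only at 0.4 with one-sided 5%

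*Protocol article*

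**What the plan says.** Section 2.7 (Sample size) of the protocol article contains these statements:

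- Size: "The study sample size target was a minimum of 40 participants". Section 2.4 gives the allocation: "Participants were randomized in a 1:1 ratio".
- Variability: the annual slope of WMH volume, as a percentage of brain volume, comes from a historical cohort with mean 0.8%, "with a SD of 0.5".
- Limit: "we have therefore chosen a noninferiority limit of 0.25, ie, the smallest difference in mean slopes between the two groups". The article then characterises this limit by the conclusion it triggers, as one "that would lead us to conclude inferiority".
- A second figure: N=40 is said to allow noninferiority to be established on about half of the historical change, that is 0.4% per year.
- Alpha: "We have applied a more liberal type I error rate (alpha, falsely declaring a difference when one does not exist) of 10" per cent. Sidedness is not given.
- Power: the formal calculation used 80%.
- Expected precision: "In practice, 95% CI for WMH volume change will be ±0.32, given the expected SD of 0.5".

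Section 2.11 says that the mixed model compares the two groups' mean rates of change and allows "estimation of average slope in each group with respective 95% CIs". Neither section says which confidence level, applied to which interval, is compared with the limit.

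**The concern.** A noninferiority conclusion needs three things that agree: one limit, one sided alpha, and the confidence interval that goes with that alpha. Section 2.7 gives two candidate limits, an alpha without a side, and an interval at a third level. The only interval it quantifies is wider than the only figure it calls the noninferiority limit.

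Alpha is also explained as wrongly declaring a difference. That is the error of a superiority test. In a noninferiority test it is the chance of declaring noninferiority when the true difference equals the limit. Similarly, failing to show noninferiority does not establish inferiority, which is what the description of the limit implies.

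At stake is the primary conclusion. For a range of plausible results, noninferiority would be shown at the stated alpha and not shown on the stated interval. If the level and the limit are still open when the data are seen, the data can choose between them.

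**Working it through.** **Inputs.** 20 per arm (N=40, 1:1; sections 2.7 and 2.4), SD of slope 0.5, limits 0.25 and 0.4, alpha 10%, power 80% (all section 2.7). Assumptions: a true difference of 0, which the article does not state, and no missing data, as the article's own ±0.32 takes the data as fully observed. Difference = rivaroxaban minus warfarin; positive is worse for rivaroxaban.

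**Step 1: reproduce ±0.32.**
SE of the difference = 0.5 × √(2/20) = 0.158.
95% half-width = t(0.975; 38 df) × SE = 2.024 × 0.1581 = 0.320. This matches the stated figure.
A single arm of 20 would give 0.234, so ±0.32 is the interval for the between-arm difference, the quantity on which noninferiority is judged.

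**Step 2: half-widths that match a 10% alpha.**
- 10% two-sided (90% CI): 1.686 × 0.1581 = 0.267.
- 10% one-sided (80% CI): 1.304 × 0.1581 = 0.206.

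Neither is 0.32. A 95% CI corresponds to one-sided 2.5%.

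**Step 3: largest observed difference that still passes** (limit minus half-width).

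| Limit | 95% CI | 90% CI | 80% CI |
|---|---|---|---|
| 0.25 | -0.070 | -0.017 | +0.044 |
| 0.4 | +0.080 | +0.133 | +0.194 |

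At limit 0.25, observed differences from -0.070 to -0.017 (10% two-sided) or from -0.070 to +0.044 (10% one-sided) pass at the stated alpha and fail on the 95% CI. At limit 0.4 the corresponding ranges are +0.080 to +0.133 and +0.080 to +0.194.

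At an observed difference of exactly 0, the upper limits are 0.32, 0.267 and 0.206. Against 0.25, only the last passes. Against 0.4, all three pass.

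**Step 4: power with 20 per arm** (noncentral t, 38 df, noncentrality = limit/SE, which is 1.58 for 0.25 and 2.53 for 0.4).

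| Limit | One-sided 2.5% (95% CI) | One-sided 5% (90% CI) | One-sided 10% (80% CI) |
|---|---|---|---|
| 0.25 | 34% | 46% | 61% |
| 0.4 | 69% | 80% | 89% |

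**Step 5: N needed for 80% power** (normal approximation, n per arm = 2 × [(z for alpha + z for power) × SD / limit]²).

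| Limit | One-sided 2.5% | One-sided 5% | One-sided 10% |
|---|---|---|---|
| 0.25 | 126 | 100 | 74 |
| 0.4 | 50 | 40 | 30 |

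Only limit 0.4 with one-sided 5% (equivalently, 10% two-sided) returns N=40. The normal approximation gives 81% power there and the t calculation 80%.

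**The case against.** The strongest reply is that nothing here is a contradiction between written decision rules. The ±0.32 is offered as expected precision and set apart from the formal calculation. The intervals in section 2.11 belong to estimation. Reporting 95% CIs beside a test at another level is ordinary practice. The choice of deciding interval is commonly left to a statistical analysis plan, which is not shown. The trial also calls itself proof-of-principle and not confirmatory.

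Most of this stands, and it limits what can be claimed:

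- A reader might infer that the plan gives two opposing noninferiority verdicts on the same data. It does not. No section makes the 95% CI the decision rule, so the mismatch is between stated error levels and limits.
- A reader might infer that an observed difference of zero must fail. That holds for limit 0.25 at 95% or 90%, but not at one-sided 10%, and not for limit 0.4 at any of the three levels.
- A reader might infer that the 10% alpha is never used. Read as two-sided, it reproduces N=40 at limit 0.4, so it can have set the sample size. It would go unused in the analysis only if the 95% CI decided.
- A reader might take 0.25 as a cut-off on the observed difference, which would give a 50% false noninferiority rate when the true difference is 0.25. The article writes no such rule.
- A reader might fault section 2.11 for giving CIs by arm only. It does say that the model compares the groups, and an article may leave the CI of the difference to the full documents.

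The reply does not remove the point. An unseen analysis plan may settle the rule, but it cannot make 0.32 smaller than 0.25, match 95% to 10%, or turn the superiority error into the noninferiority error. Those are statements made in the article itself.

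**Conclusion.** The point holds as an inconsistency within section 2.7. The ±0.32 is correct arithmetic, but it exceeds the stated 0.25 limit and matches the 10% alpha on neither reading. The stated 80% power is recovered only at 0.4 with one-sided 5%. At 0.25 the power is between 34% and 61%, depending on the level. If the 95% CI were the deciding interval, power would be 34% at 0.25 and 69% at 0.4.

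The definition of alpha is wrong for a noninferiority test however the rest is resolved. The wording about concluding inferiority is loose and should be corrected at the same time, although it does not alter the analysis by itself.

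These figures rest on SD 0.5, 20 analysed per arm, and a true difference of zero. Fewer completers or a larger SD would lower the power. The 0.25 versus 0.4 conflict has to be resolved together with the confidence level, because settling either one alone leaves the stated power unsupported or undefined.

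**What to change.** Before unblinded analysis, amend the protocol and the analysis plan as follows:

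1. Name one noninferiority limit, either 0.25 or 0.4, and remove or explain the other.
2. State one rule: noninferiority is concluded if the upper limit of the two-sided 90% CI (one-sided alpha 5%) for the difference in annual slopes, rivaroxaban minus warfarin, is below that limit. This is the level that reproduces N=40 at 0.4, and it agrees with a two-sided reading of the 10%.
3. Restate the power of N=40 for the limit kept: about 80% at 0.4, about 46% at 0.25.
4. Label the 95% CI of ±0.32 as descriptive. If 0.25 is kept, say that this interval is wider than the limit.
5. Define alpha as the probability of declaring noninferiority when the true difference equals the limit, and replace "that would lead us to conclude inferiority" with wording to the effect that noninferiority has not been shown.

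The cost is wording only; no data collection or model changes. The downside is that, if 0.25 is kept, the document must report power well below 80%, and an observed difference of zero would not show noninferiority (0.267 against 0.25). By the normal approximation, 80% power at that limit and level would need N=100.

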### Recruitment

2.8

Recruitment was monitored monthly, and staff at centers were encouraged and supported to search for suitable patients. Recruitment rates were reported regularly throughout the RISAPS recruiting period to trial oversight committees and funders. Any concerns regarding the rate of recruitment were discussed with relevant committees, and appropriate strategies were implemented.

### Assignment of interventions (allocation and blinding)

2.9

Participants were randomized by site Principal Investigator/delegate via Sealed Envelope online randomization service, with minimization by SLE status. Due to the requirements of safe anticoagulant management, treatment allocation is not blinded during the study, except at the stage of outcome analysis (brain imaging, neurologic outcomes, bleeding, and recurrent thrombotic events).

### Data collection and management

2.10

Trial data are collected via a secure online electronic data capture system, and pseudonymized clinical imaging data via a secure file transfer portal.

### Statistical methods for analyzing primary and secondary outcomes

2.11

The primary outcome will be analyzed using a linear mixed effects model to compare the mean rate of change in WMH volume over time between the two randomized groups. This will allow estimation of average slope in each group with respective 95% CIs, while allowing for variability between individuals within each group. Interparticipant clustering will be modeled by fitting a random intercept model, and measurement of differences in rates of WMH volume changes for each participant will be facilitated by introducing a random slope. The primary model will not include explanatory variables apart from the minimization variable. The fixed effects will include randomized groups only. We will restrict the sample to those who have completed the study and provided data for two MRI scans, as we do not feel that the assumptions of Missing At Random (MAR) or Missing Completely At Random (MCAR) are appropriate in this clinical context.

Further details are provided in the Supplementary File, including (i) methods for additional analyses (eg, subgroup and adjusted analyses) and (ii) definition of analysis population relating to protocol nonadherence and statistical methods to handle missing data.

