### Trial design, participants, interventions, and outcomes

2.1

The Rivaroxaban for stroke patients with APS (RISAPS) trial is a phase IIb prospective, randomized, controlled, noninferiority, open-label, proof-of-principle trial in adult patients with APS and previous ischemic stroke, TIA, or other ischemic brain manifestations. Eligible patients from participating centers in UK, after providing fully informed written consent, were enrolled and randomized 1:1 to either high-dose rivaroxaban 15 mg twice daily or high-intensity warfarin, target INR 3.5 (range, 3.0-4.0), the latter being regarded as standard of care in this study. The primary outcome for comparison of relative efficacy is the rate of change in brain WMH volume on magnetic resonance imaging (MRI), a surrogate marker of ischemic damage, between baseline and 24 months follow-up between these 2 treatment arms.

The study design was amended from phase II/III to phase IIb following revision of sample size target from 140 to 40 participants (minimum). This was necessitated by adverse recruitment factors, including in relation to the COVID-19 pandemic and decision to exclude triple-aPL-positive patients.

The official title of the trial is: Rivaroxaban vs Warfarin for Stroke Patients With Antiphospholipid Syndrome, With or Without SLE (RISAPS): a Randomised, Controlled, Open-label, Phase IIb, Non-inferiority Proof of Principle Trial.

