1. Bleeding: The number of all bleeding events: major, clinically relevant nonmajor, minor per person, as well as the number of these events overall 2. The Number of serious adverse events other than major bleeding per person as well as the number of these events overall 3. The number of cerebral microbleeds assessed with susceptibility-weighted imaging as a surrogate marker of bleeding risk per person as well as the number of these events overall
C. Health economics
1. Quality of life assessed using 5-level EQ-5D-5L 2. Health and social care resource use assessed using trial follow-up visit case report forms 3. Mean incremental cost per quality-adjusted life year
D. Anticoagulation intensity
1. Rivaroxaban i) Rivaroxaban concentration measured with an amidolytic anti-Xa assay
2. Warfarin i) Time in target INR therapeutic range ii) Factor X level measured with an amidolytic factor X assay (LA independent assessment of warfarin anticoagulant effect)
E. Exploratory outcomes
1. Rivaroxaban pharmacokinetic modeling 2. Cerebral blood flow derived from MR perfusion imaging using an arterial spin labeling technique

INR, international normalized ratio; LA, lupus anticoagulant; MR, magnetic resonance.

RISAPS uses a single scanning site for baseline and outcome MRI brain scans in all trial participants so as to optimize reproducibility and minimize variability in assessment of neuroradiological biomarkers.

To ascertain whether APS patients have a different PK rivaroxaban profile compared with other populations where rivaroxaban is prescribed, we will develop a population PK model for rivaroxaban as part of the RISAPS trial.

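### With two scans per participant, the random slope in the primary model cannot separate individual progression from scan error and makes the fit unreliable

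*Protocol article*

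**What the plan says.** Section 2.11 of the protocol article builds the primary model in two steps. First, "Interparticipant clustering will be modeled by fitting a random intercept model". Then a random slope is added, with the stated purpose that "measurement of differences in rates of WMH volume changes for each participant will be facilitated by introducing a random slope". On fixed effects it says "The fixed effects will include randomized groups only", next to a sentence that admits the minimization variable (SLE status). The analysis set is limited: "We will restrict the sample to those who have completed the study and provided data for two MRI scans".

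Section 2.1 places the comparison "between baseline and 24 months follow-up between these 2 treatment arms". Section 2.5 speaks only of a baseline and an outcome scan: "RISAPS uses a single scanning site for baseline and outcome MRI brain scans in all trial participants". No intermediate scan is described. The schedule figure is not reproduced in the text available, but the two-scan restriction is explicit.

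Section 2.11 gives no covariance structure for the random effects and no constraint on the residual. It refers further details to a Supplementary File that is not available here. Section 2.7 gives the size: "The study sample size target was a minimum of 40 participants".

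**The concern.** A random slope is useful when each person has enough measurements for departures from their own line to be seen. With two points the line passes through both, and nothing is left over to estimate scan error. With 40 participants there are 80 observations and, under this model, 80 random effects.

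Two things are at stake. The stated purpose of the random slope, to measure differences in individual rates, is not something the design can deliver. And software asked to maximise a likelihood with a flat ridge may fail to converge, stop on a boundary, or report an unreliable standard error. Noninferiority is judged from the confidence interval for the slope difference, so a poor standard error bears on the main conclusion.

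**Working it through.** **Inputs.** From the article: two scans per analysed participant (section 2.11); baseline and 24 months, so T = 2 years (section 2.1); 40 participants at 1:1, so 20 per arm (sections 2.7 and 2.4); SD of annual slope 0.5 and 95% CI half-width ±0.32 (section 2.7). Assumed: the variance values below, and that the model contains time and group-by-time terms, since a slope difference is otherwise not a parameter.

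**1. The article's precision figure.** t(0.975, 38 df) × 0.5 × √(2/20) = 0.320. This reproduces ±0.32 as the half-width for a difference in mean slopes with 20 per arm.

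**2. Counting.** Let a = intercept variance, b = slope variance, c = their covariance, e = residual variance. Then:

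- Var(baseline) = a + e
- Cov(baseline, 24 months) = a + Tc
- Var(24 months) = a + 2Tc + T²b + e

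That is three equations in four unknowns. The Jacobian has rank 3 of 4.

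**3. Example with T = 2 and an assumed baseline variance of 4.**

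| a | b | c | e | Var(baseline) | Cov | Var(24 m) | slope SD = √b |
|---|---|---|---|---|---|---|---|
| 4.0 | 0.25 | 0 | 0 | 4 | 4 | 5 | 0.50 |
| 3.9 | 0.20 | 0.05 | 0.1 | 4 | 4 | 5 | 0.45 |
| 3.8 | 0.15 | 0.10 | 0.2 | 4 | 4 | 5 | 0.39 |
| 3.6 | 0.05 | 0.20 | 0.4 | 4 | 4 | 5 | 0.22 |

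All four rows have the same likelihood, so the data cannot choose among slope SDs from 0.22 to 0.50.

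**4. What stays fixed.** The variance of annualised change is b + 2e/T². In the four rows it is 0.25 + 0, 0.20 + 0.05, 0.15 + 0.10 and 0.05 + 0.20, which is 0.25 each time (SD 0.5). The SE of the slope contrast is therefore the same in every row, and the half-width is 0.32 throughout.

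**5. Other readings of the model.**

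- Uncorrelated random effects (c = 0): three parameters, rank 3 of 3. This is just identified, but only by assuming that progression is unrelated to baseline WMH burden.
- Actual scan times spread over an assumed 1.9 to 2.2 years: rank 4 of 4, but weakly identified (condition number 82).

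**6. One simulated data set, 20 per arm.** The change score gave a slope difference of -0.10806 (SE 0.2573), and a random-intercept-only model gave the same. The correlated random-slope model gave the same estimate under four optimisers. Three reported convergence, at a log-likelihood of about -154.507, with residual variances of 0.668, 0.657 and 0.385 and an SE of 0.2573, 0.2573 and 0.2571. The fourth did not converge and reported 0.2510.

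**7. Repeated fits.** I took 100 simulated trials of 20 per arm, using the third row of the table as the truth and fitting the correlated model by REML with one package's default settings (statsmodels).

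- 93 fits gave a convergence, singularity or boundary warning.
- The slope-difference estimate always equalled the change-score estimate.
- The reported SE was 0.995 to 1.64 times the change-score SE. It was more than 5% off in 65 fits and more than 20% off in 48.

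A further 40 default fits agreed: 85% gave warnings, about a third converged, and 70% had an SE more than 5% off (up to 1.42 times). In one rerun of 40, 13 fits were flagged as converged, and about 30% of those still had an SE more than 5% off. A second optimiser converged in only 4 of 40, and those four SEs were correct.

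**8. Scale.** A 20% inflation takes ±0.32 to 0.32 × 1.20 = ±0.38. A factor of 1.42 takes it to 0.32 × 1.42 = ±0.45.

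**The case against.** The strongest reply is that the primary estimand is a contrast of mean slopes, not a variance component. With complete pairs at common times it equals the difference in mean annualised change. A properly maximised fit returns that estimate with the right SE. This stands, and steps 4 and 6 show it.

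Three stronger readings are tempting, and the documents do not support them.

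- **That the primary model cannot be estimated at all.** Non-identifiability holds for correlated random effects at common scan times. The article does not say that the effects are correlated; the uncorrelated form is just identified, and varying dates give weak identification. The treatment contrast is estimable in every case.
- **That a wrong zero-covariance constraint makes the SE wrong.** The zero-covariance model was fitted to data with true intercept-slope correlations of -0.5, 0, 0.3 and 0.5 (150 data sets each, assumed variances). The SE matched the change-score SE with a mean ratio of 1.000 in every setting. In the single data set of step 6, where this model stopped at a residual variance of zero, the SE was 0.2615 against 0.2573, a ratio of 1.016.
- **That a constraint would be chosen after the data are seen.** The analysis plan and the Supplementary File are not available here and may fix the covariance structure and a fallback. Their absence from a journal article is not itself a fault.

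The last reply does not remove the point. The article does state a random slope, does restrict the sample to two scans, and does say what the random slope will deliver. One reading of that text is unidentified, and the other needs an assumption that the text does not state.

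**Conclusion.** The point holds as a mismatch between a stated model and the design. Two scans cannot separate true variation in individual slopes from scan error, and the correlated random-slope model has four variance parameters on three moments. There is no bias in the treatment contrast and no necessary error in its SE.

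The practical risk is a failed fit or a misreported SE. In the simulations described, more than half of the default fits reported an SE more than 5% off. In the 100-trial set the range of 0.995 to 1.64 means that every such error was an inflation. Under those settings the likelier harm is an interval that is too wide and a missed noninferiority conclusion, rather than a false claim. The non-converged fit in step 6 erred the other way, by about 2% (0.2510/0.2573 = 0.976).

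The counting argument rests on common scan times and correlated effects. The failure rates rest on assumed variances and one package, and other software will differ.

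**What to change.** Drop the random slope from the primary model and choose one of two forms that two scans can support:

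- a linear model for annualised change (24-month minus baseline volume, divided by the actual interval) on randomized group and SLE status; or
- a two-visit repeated-measures model with an unstructured 2×2 covariance, in which the group-by-time term is the treatment effect. For this to adjust the slope for SLE status as the first form does, it needs an SLE-by-time term, because a main effect adjusts only the level.

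Remove the statement that the random slope measures each participant's rate. If the analysis plan or Supplementary File already fixes one of these forms, it is enough to bring the published description into line.

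The cost is wording, settled before unblinded analysis. The slope contrast is the same with complete pairs at common times, the fit is simpler, and no sample-size figure changes.
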